## Abstract

**Background:**

Older adults with cognitive problems have a higher risk of falls, at least twice that of cognitively normal older adults. The consequences of falls in this population are very serious: fallers with cognitive problems suffer more injuries due to falls and are approximately five times more likely to be admitted to institutional care. Although the mechanisms of increased fall risk in cognitively impaired people are not completely understood, it is known that impaired cognitive abilities can reduce attentional resource allocation while walking. Since cognitive enhancers, such as cholinesterase inhibitors, improve attention and executive function, we hypothesise that cognitive enhancers may reduce fall risk in elderly people in the early stages of cognitive decline by improving their gait and balance performance due to an enhancement in attention and executive function.

**Method/Design:**

Double blinded randomized controlled trial with 6 months follow-up in 140 older individuals with Mild Cognitive Impairment (MCI). Participants will be randomized to the intervention group, receiving donepezil, and to the control group, receiving placebo. A block randomization by four and stratification based on fall history will be performed. Primary outcomes are improvements in gait velocity and reduction in gait variability. Secondary outcomes are changes in the balance confidence, balance sway, attention, executive function, and number of falls.

**Discussion:**

By characterizing and understanding the effects of cognitive enhancers on fall risk in older adults with cognitive impairments, we will be able to pave the way for a new approach to fall prevention in this population. This RCT study will provide, for the first time, information regarding the effect of a medication designed to augment cognitive functioning have on the risk of falls in older adults with Mild Cognitive Impairment. We expect a significant reduction in the risk of falls in this vulnerable population as a function of the reduced gait variability achieved by treatment with cognitive enhancers. This study may contribute to a new approach to prevent and treat fall risk in seniors in early stages of dementia.

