#### Falls

A fall is defined as 'an unintentionally coming to rest on the ground, floor, or other lower level and not due to a seizure or an acute stroke [63]. Recurrent falls are defined as two or more events in a six-month period during the trial. An absolute reduction of 10 points in the rate of falls is expected in intervention group after six months of follow-up (20% in the control to 10% in the intervention). Because falls tend to be forgotten if no injuries are involved, a fall calendar enabling prospective assessment will be implemented [64]. At the baseline session, participants will receive a fall calendar and instructed in its use (i.e. they will be asked to record every day whether they have had a fall). Each monthly calendar page detaches along a perforation and becomes a postage-paid postcard addressed to the study office. Calendar pages each have a unique study ID number and no identifying information. If a calendar is not received by two weeks into the following month, or is missing or incomplete the research assistant will contact the participant by phone and together they will complete the page. Participants who indicate one or more fall will be contacted by study staff and interviewed about the circumstances and outcomes of the falls. These methods have been used locally in previous research [47,48].

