### Sample size determination

Sample size determination is based on our primary outcomes and using the values from the pilot data described above. We expect a 10% improvement in gait velocity (G-vel), measured in cm/s (effect size of 0.10 m/s, from 1.0 m/s to 1.10 m/s), and a reduction in gait variability (G-var) (stride time variability) of 10% as assessed by decreases in standard deviation and coefficient of variation. These expected changes are based on our preliminary data which showed that mean G-vel increased by 15% after one month of treatment and these changes were sustained and improved in the 4 months follow up [38]. In this study, we found that the mean stride time at usual gait was 1190 ± 266 milliseconds (ms), after one month of treatment was 1053 ± 178 ms, and after 4 month was 999 ± 112 ms. The absolute reduction of the mean group CoV was 11 points (from 22.4% to 11.3%). Therefore, it is reasonable to expect similar improvements in our proposed study with a larger sample. Thus, in order to detect a group reduction of variability of 10% with a type II error of 0.20, 69 participants in each arm will be needed for the final analysis; assuming a 5 percent drop-out rate (which was seen after 6 months in two previous studies testing medications on MCI), 75 per arm participants will need to be recruited. This sample will also allow the detection of a 10% difference in the mean scores of the ABC, which is considered clinically significant. While we will not have sufficient power for a definitive analysis of changes in fall rate or risk, we will be able to compare changes in the mean values of the primary outcomes with between-group differences in fall rate. This will add mechanistic evidence that changes in fall rate are due to changes in gait parameters, and will provide a point estimate needed for the sample size calculations for a future trial powered to detect a reduction in falls as a primary endpoint.

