### Statistical Analysis

Analyses will be performed according to an intention-to-treat principle. Baseline characteristics and gait parameters will be descriptively summarized using either means and standard deviations or frequencies and percentages, as appropriate. Comparisons of the changes in the mean balance confidence score will be assessed using *t*-test. The coefficient of variation [CoV = (SD/mean)*100] will be used to quantify gait variability. We will use linear regression to perform between-group comparisons using three data points (baseline, one month, six months) with baseline – 1 mo. corresponding to before treatment and 1 mo. – 6 mo. corresponding to treatment with donepezil. Linear regression models, both unadjusted and adjusted for age, sex, and history of falls, will be used for comparison of individual variables. Using the baseline value of an endpoint as a covariate is more powerful statistically than comparing the differences from baseline. The statistical significance of the results will be determined by Hochberg's variation of the Bonferroni procedure for multiple testing [65]. Two-sided *p *< 0.05 will be considered statistically significant. All calculations will be made using SPSS software package version 16.0 (SPSS Inc., Chicago, IL).

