## Discussion

Elderly adults with cognitive problems are one of the most vulnerable sectors of our society with clear mental, social, and physical disadvantages. They are more likely to experience falls, and experience further mobility decline due to having fallen; therefore is an urgent need to identify evidence based interventions for reducing the risk of falls and related injuries in people with cognitive impairment. To date, no adequately- powered studies have investigated the effect of cognitive enhancers to reduce falls in people with MCI. As falls are one of the most common reasons for both hospital admissions and nursing home placements in older adults with cognitive difficulties, they contribute significantly to the overall health care burden for Canada.

This study is distinctive due to the fact the intervention will target cognition with the outcome to improve mobility, balance, gait performance, and risk of falls. If we can demonstrate the effect of cognitive enhancers on fall risk and gait performance, these results will reveal a previously unrecognized benefit of this pharmacological therapy, which could in turn serve to decrease this burden. We are a unique position to conduct this project based on our previous research program expertise with gait assessment as well as our record of research involving elderly people with MCI

By characterizing and understanding the effects of cognitive enhancers on fall risk in older adults with cognitive impairments, we will be able to pave the way for a new approach to fall prevention in this population. This RCT study will provide, for the first time, information regarding the effect of a medication designed to augment cognitive functioning have on the risk of falls in older adults with Mild Cognitive Impairment. We will expect a significant reduction in the risk of falls in this vulnerable population as a function of the reduced gait variability achieved by treatment with cognitive enhancers. In this vein, we would establish that medications that augment cognitive function could be a complementary therapeutic option for reducing fall risk in people with MCI. This may contribute to a new approach to prevent and treat fall risk in this population, which will lead to improving the autonomy and quality of life of seniors in early stage of dementia.

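### The article expects a significant fall reduction at about 38% power on its own fall rates, and attributes fall changes to gait from a comparison that cannot show it

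*Protocol article*

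**What the plan says.** Falls are a secondary outcome, as total number by month six and as proportion of participants who fall (Secondary outcomes). Three statements about them matter here.

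- **Expectation.** The discussion paragraph of the Abstract states: "We expect a significant reduction in the risk of falls in this vulnerable population as a function of the reduced gait variability". The main Discussion repeats it: "We will expect a significant reduction in the risk of falls in this vulnerable population".
- **Size.** The Falls section states: "An absolute reduction of 10 points in the rate of falls is expected in intervention group". The rates given are 20% in control and 10% in intervention over six months.
- **Power and mechanism.** Sample size determination concedes: "While we will not have sufficient power for a definitive analysis of changes in fall rate or risk". It says the trial will yield a point estimate for sizing a later falls trial. It also proposes to compare changes in the mean primary (gait) outcomes with the group difference in fall rate, and concludes: "This will add mechanistic evidence that changes in fall rate are due to changes in gait parameters".

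On models, Statistical Analysis ties the t-test to the balance confidence score and adds: "Linear regression models, both unadjusted and adjusted for age, sex, and history of falls, will be used for comparison of individual variables". No model is assigned to falls.

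**The concern.** The Abstract and Discussion forecast a result that the sample size section says the trial cannot be relied on to deliver. A reader of the Abstract alone would take a non-significant fall result as evidence against the drug. In fact it would be the more likely result even if the expected halving were true.

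The mechanism sentence concerns what the trial may conclude. If gait improves and falls decrease in the donepezil arm, the text as written licenses the statement that the second happened because of the first. Randomisation supports an effect of donepezil on gait and an effect of donepezil on falls. It does not by itself support an effect of gait on falls.

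**Working it through.** **Inputs**

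- Fall rates 0.20 and 0.10, read as proportions of fallers (Falls).
- Two-sided 0.05 (Statistical Analysis) and 1:1 allocation (Randomisation).
- 69 per arm analysed and 75 per arm recruited (Sample size determination). The Design section gives 140 in total, or 70 per arm.

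**The plan's own figure.** The article states no power for falls. Its 69 per arm is for a 10% reduction in gait variability at 80% power. It cannot be reproduced because no between-person SD of gait variability is given. It implies a standardised effect of √(2/69) × (1.960 + 0.842) = 0.477. I take 69 as given.

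**Power for falls, two proportions with pooled null variance**

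- Mean proportion: (0.20 + 0.10)/2 = 0.15.
- SE under the null: √(2 × 0.15 × 0.85/69) = 0.0608.
- SE under the alternative: √((0.20 × 0.80 + 0.10 × 0.90)/69) = 0.0602.
- Power: Φ((0.10 − 1.96 × 0.0608)/0.0602) = Φ(−0.318) = 37.5%.

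| Analysed per arm | Power |
|---|---|
| 66.5 (70 less 5% drop-out) | 36.4% |
| 69 | 37.5% |
| 70 | 38.0% |
| 75 | 40.2% |

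At 69 per arm the unpooled formula gives 38.3%, the arcsine formula 38.5%, exact enumeration of the chi-square test 37.6%, and Fisher's exact test 29.9%. Across 66 to 75 per arm, no two-sided version exceeds about 41%. If 0.20 and 0.10 are instead read as falls per person (an assumption), a Poisson comparison at 70 per arm has 32% power. A negative binomial with assumed dispersion 0.5 to 2 has 30% to 26%.

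**Size for 80% power.** (1.96 × √0.255 + 0.842 × √0.25)² / 0.10² = 199 per arm.

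**What the expected result would look like.** The 95% half-width is 1.96 × 0.0602 = 11.8 points. An observed 10-point reduction would therefore have an interval from about −2 to +22 points. In counts, 14 of 69 against 7 of 69 gives a pooled proportion of 21/138 = 0.152, SE √(0.152 × 0.848 × 2/69) = 0.0612, z = 0.1014/0.0612 = 1.66 and p of about 0.10. The expected result is itself not significant.

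**Mechanism.** No arithmetic is needed.

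1. With two arms, the proposed comparison sets one gait contrast beside one fall contrast. Two arm-level points always lie on a line, so the comparison has no residual information with which to test whether gait carries the effect.
2. The same pair of contrasts arises if donepezil reduces falls entirely through gait, or if it improves gait and reduces falls by another route.
3. The plan itself names other routes. Hypothesis 2 concerns balance and balance confidence, and the mechanistic hypothesis concerns attention and executive function. The Background also describes a cholinergic motor effect not mediated by cognition.
4. Objective 3 covers mediation from cognition to gait and balance. No stated objective tests the step from gait to falls, which Hypothesis 1 asserts.

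**The case against.** The strongest reply is that the methods text is candid. Low power for falls is conceded, falls are secondary, and the stated use is a planning estimate. The Abstract and Discussion wording changes no sample size, analysis or decision rule. This stands in part: a reader might infer that the shortfall is concealed, and it is not. But the caveat is missing where the expectation is stated, and the two cannot both stand.

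It can also be said that the word significant is not tied to a p-value, and that the article uses fall risk for surrogates such as sway and balance confidence. This helps little. The sentence names a reduction in the risk of falls as a consequence of reduced gait variability, and the Falls section attaches 20% and 10% to falls themselves.

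On mechanism, the text claims to add evidence, so reading it as a promise of proof goes too far. The objection to the causal wording remains, because the comparison described does not bear on that causal step.

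Two stronger readings should be set aside:

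- **That falls will be analysed by t-test or linear regression.** The t-test belongs to balance confidence, and the regression text follows the definition of gait variability and discusses baseline covariates and three time points. A fall model may sit in the full protocol or statistical analysis plan, so its absence here is no finding. The reference to individual variables is loose and could usefully be narrowed.
- **That standard errors from a wrong model would feed the next trial.** The article carries forward a point estimate, and assigns no such model to falls.

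**Conclusion.** The point holds in two parts.

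1. The stated expectation of a significant fall reduction conflicts with the article's own rates and with its own admission. Power is about 38% at 69 per arm and about 40% at 75, against 199 per arm needed for 80%. If the expected halving is real, the trial would still miss significance about 62% of the time (100 − 37.5 = 62.5). This rests on reading 20% and 10% as proportions of fallers, a single two-sided 0.05 test and near-complete follow-up. Reading them as rates lowers the power. So would any multiplicity adjustment that includes falls.
2. The claim that fall changes are due to gait changes does not follow from comparing group means in a two-arm trial, whatever its size.

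Both are faults of stated expectation and inference about a secondary outcome. They do not affect the primary gait comparisons. They still matter because fall prevention is the trial's main rationale.

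**What to change.** - **Abstract and Discussion:** replace the expected significant reduction with a statement that the effect on falls will be estimated with a 95% confidence interval and that the trial is not powered to show a significant reduction. This matches Sample size determination.
- **Sample size determination:** delete the sentence attributing fall changes to gait. If mechanism is to be kept, replace it with a participant-level mediation analysis adjusted for baseline and labelled exploratory. Gait should be measured before the falls it is meant to explain, for example at month one. Gait itself is not randomised and fallers will be few (69 × 0.20 + 69 × 0.10 = about 21), so such an analysis would be imprecise and open to confounding.
- **Statistical Analysis, optional:** say that linear regression of individual variables is meant for the continuous outcomes and not for fall counts or faller status.

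The cost is a few sentences and a more modest stated claim. Sample size, visits and data collection do not change.

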**Trial Registration:**

The protocol for this study is registered with the Clinical Trials Registry, identifier number: NCT00934531 http://www.clinicaltrials.gov

## Background

### Cognitive Decline and Falls: A well-known couple

An important goal of geriatric medicine is to reduce the gap between life expectancy and disability-free life expectancy. A substantial portion of this gap is caused by two major geriatric syndromes: cognitive impairment and mobility limitation, which ultimately manifest as dementia and falls, respectively. Interestingly, these manifestations often coexist in elderly people: falling is a common geriatric syndrome affecting about a third of older adults each year, and dementia has a prevalence of 8% of Canadians aged 65 and 35% in people over age 85 [1-3]. This interrelationship has been attributed to specific brain networks selectively affected by diseases that accompany, but are not necessarily caused by, ageing [4].

Older adults with cognitive problems have a higher risk of falls, with annual incidence of around 60–80%; at least twice that of cognitively normal older adults [5]. The consequences of falls in this population are very serious; fallers with cognitive problems are approximately five times more likely to be admitted to institutional care than people with cognitive issues who do not fall [6]. They are also at high risk of major fall-related injuries such as fractures and head injuries leading to increased mortality. Falls are a major cause of disability and dependence in older people, and more so for those with cognitive problems. In addition to indirect costs and caregiver burden, the direct costs of emergency, acute, rehabilitation and long-term care are substantial and increasingly unsustainable for the health care system. Although the mechanisms of increased fall risk in cognitively impaired people are not completely understood, it is known that impaired cognitive abilities can reduce attentional resource allocation while walking [7]. As well, since executive function is an important cognitive resource for normal walking, impairments in this domain are also associated with both dementia and risk of falls [8].

One approach to mitigating fall risk in people with memory problems is to target them in the early stages of cognitive decline. Mild Cognitive Impairment (MCI) is a recognized clinical entity that is a transitional state between benign age-related cognitive change and early dementia. Specific diagnostic criteria have been developed and validated [9-13] to diagnose MCI, with the prevalence of the diagnosis being estimated at 19% among older adults, increasing to 29% in those over age 85 [14]. People with MCI have been found to have a 10 to 15 times higher risk of developing Alzheimer's disease (AD), as well as a higher risk of falling compared with age-matched controls [15,16].

### The role of cognition on gait: The dual-task paradigm and gait variability

Although walking has long been considered primarily as an automatic motor task, emerging evidence suggests that this view is overly simplistic [17]. Cognitive function may play a key role even in the regulation of routine walking, particularly in older adults. Attention is a necessary cognitive resource for maintaining normal walking and there is evidence that cognitive and attentional deficits are independently associated with postural instability, impairment in performing daily living activities, and future falls [8]. The role of cognition in walking is even more marked in people with cognitive dysfunction, whose gait performance is affected by any extra cognitive load. Since Lundin-Olsson and colleagues' seminal "stops walking while talking" study [18] demonstrated that the inability to maintain a conversation while walking is a marker for future falls in older adults, observing people walking while they perform a secondary task ("dual-task paradigm") has become the accepted way to assess the interaction between cognition, gait, and risk of falling. Previous research on the effect of dual-tasking on gait performance showed specific associations between slowing gait and executive dysfunction and attention deficits [15,17,19-25]. In a previous study, we assessed 60 elderly individuals with MCI and found that impairments in several cognitive domains (attention, executive function, and working memory) are associated with both a slow usual gait velocity and slower gait velocity under dual-task conditions, demonstrating that these specific cognitive domains are crucial for maintaining normal gait performance [26].

A sensitive measure of gait performance is gait variability, defined as the stride-to-stride variation in time [27]. This measure quantifies the automaticity of gait, with greater variability indicating less rhythmicity and a more unstable gait pattern. Evaluating gait variability is an accurate methodology to identify subtle changes in walking due to pathological conditions or disease. For instance, cognitively normal older adults have low gait variability; however, high gait variability has been described in Parkinson's disease, Alzheimer disease, and has been associated with high risk of future falls and mobility decline [28]. Additionally, previous studies have demonstrated that gait variability may serve as a clinically relevant parameter in the evaluation of mobility, and may be a responsive measure for different interventions in fall prevention [29].

### There is a lack of effective strategies for preventing falls in older people with memory problems

Previous trials in cognitively normal older adults have demonstrated that both multifactorial (e.g. review of medications, strength and balance training, visual and hearing corrections, and environmental modifications) and some single interventions (resistance and balance exercises) are effective in preventing falls [30]. By contrast, most of the studies targeting falls in people with cognitive problems have been unable to prevent falls [31-33].

A recent systematic review and meta-analysis [31] concluded that the benefit of these single and multifactorial interventions does not translate from cognitively normal older adults to those with dementia. It is possible that different underlying mechanisms are at work in those with dementia; thus, a different approach may be necessary to target fall risk in this population. Although much is known about the multifactorial nature of falls in cognitively normal individuals, knowledge about the nature of falls in those with cognitive problems is limited and as a consequence, the number of falls and fall related injuries in this population continues to increase [33].

